#### Primary hypothesis/primary outcome

The primary hypothesis is that folic acid supplementation of 4 mg/day at preconception and during the first three months of pregnancy will decrease the recurrence of NSCL/P in a high risk (history of NSCL/P in mother or child) group of women when compared to women taking 0.4 mg per day of folic acid. The primary outcome measure will be the difference in NSCL/P recurrence rates between the two groups and the associated confidence interval. The study is powered to detect a 50% reduction at a 0.8 power.

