#### Related risks

Potential risks involved in this study include those of blood drawing and interview participation, which are felt to be minimal. Folic acid supplementation has overall three aspects that have already been discussed in the literature:

1. The use of folic acid may mask vitamin B12 deficiency in cases of pernicious anemia and cause irreversible neurological damage. In order to avoid this effect, a B12 assay on every subject will be performed prior to folic acid administration, and every year thereafter. Complete blood tests will be performed on collected samples at enrollment to help detect anemia. Current exposure to folic acid through fortification in the US has been reported not to increase the risk of masking anemia
[122]. This does not imply though that high doses of folic acid do not necessarily increase the masking risk, mainly for cases with B12-deficiency related neuropathy with no anemia. Yet due to the small percentage of subjects expected to have B12 deficiency, the assessment of B12 levels on a yearly basis after supplementation provides an appropriate strategy to monitor subject safety related to this issue. The added cost compared to added benefit of more frequent blood sampling to measure B12 (or other analytes) is considered high in terms of increasing the burden on subjects and lowering motivation that it should be avoided.

2. It has been suggested in the literature, though not confirmed, that high folic acid doses, such as the one used in the present study, may increase the risk of spontaneous abortions (expected spontaneous abortion rate = 15%). The numbers of spontaneous abortions will be reported and the Data Safety Monitoring Board (DSMB) will determine whether these exceed the threshold for an adverse event.

3. It has been suggested in the literature, though not confirmed, that folic acid increases twinning. Should a pregnancy result in twins, twin pregnancies in general have an increased risk of premature delivery with an intendant risk of increased mortality and morbidity for the infant, and also an increased risk of maternal complications including pre-eclampsia. Therefore, information on this matter will be collected, and the DSMB will evaluate whether the rate of twinning exceeds the threshold for an adverse event.

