#### Primary and secondary outcome measures

##### Primary outcome measure

The primary outcome assessed is a measure of recurrences of NSCL/P in offspring of the trial mothers. All live born children born of at least 500g or gestation of 24 weeks or beyond with NSCL/P (only Tessier X clefts included) will be identified by case finding and verified by in person clinical exam. For the classification of cleft lip and cleft palate malformations, the following schemata taken from the Division of Plastic Surgery and Burns of the Department of Surgery of the University of Sao Paulo Medical School, Brazil will be used in Table
6.

**Table 6 T6:** Classification of cleft lip and cleft palate malformations:

**Group I**	**Pre-incisor foramen clefts (Clefts lying anterior to the incisor foramen). Clefts of the lip with or without an alveolar cleft.**	
	a) Unilateral	
	Right	Total – when they reach the alveolar arcade
	b) Bilateral	Partial
		1) Total}On one or both sides
		2) Partial
	c) Median	1) Total
		2) Partial
Group II.	Trans – incisor foramen clefts (Clefts of the lip, alveolus and palate)	
	a) Unilateral	Right
		Left
	b) Bilateral	
Group III.	Post-incisor foramen clefts (Clefts lying posterior to the incisor foramen)	
	1) Total	
	2) Partial	
Group IV.	Rare facial clefts	

*Taken from Division of Plastic Surgery and Burns of the Department of Surgery of the University of Sao Paulo Medical School, Brazil (Spina* et al.*, 1972).*

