As secondary analyses, we will check for potential selection bias in the sample of subjects who contribute informative data for analysis (e.g. births or folate levels) due to non-random choices of subjects to participate in the study or to get pregnant and/or give birth (mainly relevant for the primary hypothesis), resulting in informative sample censoring. The issue of concern is not a biased estimate of the intervention effect in the used data samples (randomization solves this problem), but whether these effects are related to any non-randomness in the nature of the used sample. Given the limited availability of data on important characteristics for potential subjects who do not respond to the invitation to participate (refuse to participate, not located, etc.) across the sites, we will analyze dropouts and absence of informative births as potential processes for sample selection bias. We will estimate separate models using logistic regression for propensity to continue enrollment in the study versus dropping out and for giving birth versus dropping out or participation without giving birth. This will be done as a function of characteristics that may affect these propensities such as age, marital status, schooling level, employment status, fertility preferences (child wantedness, contraceptive use), cleft risk group (woman with a cleft or mother to a child with a cleft), previous fertility history (e.g. number of previous children), and area of residence. Data is collected on all these characteristics at enrollment. The propensities will be used as inverse probability weights for the analyses of effects of intervention on study outcomes. The propensities for giving birth will apply to the outcomes measured among study births (cleft recurrence and severity, birthweight, gestational age, etc.) while those for maintaining enrollment will apply to outcomes measured at the subject level (e.g. folate levels). For pregnancy-level outcomes, such as miscarriage, twinning, and pre-eclampsia, propensities for pregnancy (in reference to dropping out or participating without getting pregnant) can be estimated.

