#### Power analysis

Table
8 presents estimates of prospective number of births in the two study groups required for 70 and 80% statistical power and 30, 50, and 70% reductions in CL/P recurrence for alternative recurrence rates of 3, 5, and 7% in the 0.4 mg group. The 30% reduction represents a lower effect that is still very clinically significant, while the 70% represents an effect similar to that observed for NTD recurrence
[118]. The recurrence rates cover most of those reported in the literature and we use the 5% rate as a primary reference for our total suggested sample size given that it represents a proportional estimate of the 4 and 7% recurrence rates assuming that 30% of the study subjects will be women with clefts and 70% will be mothers to children with clefts. The power calculations are based on a Type I error probability of 5%. We use a one sided test as the recurrence rate in the 4 mg is not expected to exceed that of the 0.4 mg group given the converging evidence of protective effects of folic acid; a Fisher’s exact test is used.

**Table 8 T8:** Power analysis for primary hypothesis

**Baseline recurrence rate**	**% Reduction**	**Power**	**Total births**	**Total subject years**
*0.07*	70	0.8	524	5475
		0.7	418	4368
	50	0.8	1114	11641
		0.7	874	9133
	30	0.8	3324	34734
		0.7	2574	26897
*0.05*	70	0.8	742	7753
		0.7	590	6165
	50	0.8	1582	16531
		0.7	1240	12957
	30	0.8	4734	49467
		0.7	3666	38307
*0.03*	70	0.8	1254	13103
		0.7	996	10408
	50	0.8	2676	27962
		0.7	2096	21902
	30	0.8	8024	83845
		0.7	6210	64890

For a 50% reduction in a baseline rate of 5% recurrence, a total of 1582 births distributed equally across the two treatment groups are required. This number of births also provides acceptable power (0.75) to detect a 60% decrease in a 3% baseline recurrence rate, or a 40% decrease in a 7% baseline risk. If the 4 mg dose shows a preventive effect similar to that seen for NTDs (70%), the required numbers of births are halved regardless of the baseline recurrence risk (range from 524 to 1254 births for 80% power). The numbers of births required to observe a 30% reduction are about three times as large those for a 50% reduction.

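### Randomisation does not protect a comparison restricted to live births: if the higher dose affects survival of affected fetuses, loss can look like prevention, and no planned analysis ties losses to the primary result

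*Protocol article*

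**What the plan says.** Under Statistical analysis, Analysis plan, the protocol calls the first analysis intention to treat but includes only randomised women who supply an informative observation, such as a birth. The Primary outcome measure section defines the cases in live births: "All live born children born of at least 500g or gestation of 24 weeks or beyond with NSCL/P".

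The Analysis plan then takes up selection, framed as women's non-random choices to take part, become pregnant or give birth. It states: "The issue of concern is not a biased estimate of the intervention effect in the used data samples (randomization solves this problem"). What remains, on this view, is only whether the effect is specific to the kind of women who end up in the sample. Logistic models for staying enrolled and for giving birth supply inverse probability weights: "This will be done as a function of characteristics that may affect these propensities such as age, marital status, schooling level", and further enrolment characteristics.

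The Related risks section says, as an unconfirmed suggestion from the literature, that high doses such as the study's "may increase the risk of spontaneous abortions (expected spontaneous abortion rate = 15"%).

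Fetal loss is followed in several places. No increase in miscarriage is a secondary hypothesis, defined in Table 7 and sized in Table 9. The monitoring board reviews adverse events by arm. Loss material is examined for clefts when available, and forms FA09&10 record the result.

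**The concern.** Randomisation makes the arms comparable among all women randomised. About 1,582 births are sought from about 6,000 women, roughly 26%. Conceiving and carrying to live birth both happen after treatment starts. If the dose changes the chance that a fetus survives, and more so for a fetus with a cleft, the two groups of live births are no longer comparable. An affected fetus lost in the 4 mg arm leaves both numerator and denominator, and the live-birth rate falls exactly as if a cleft had been prevented.

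The stated reasoning rules this out by assertion, in a document that elsewhere names fetal loss as a possible effect of the higher dose. At stake is the meaning of a positive result in a trial that hopes to set the standard of care for high-risk women.

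**Working it through.** **1. The plan's own figure.** Inputs from Power analysis: "For a 50% reduction in a baseline rate of 5% recurrence, a total of 1582 births"; a type I error of 5%; Fisher's exact test; and "We use a one sided test as the recurrence rate in the 4 mg is not expected to exceed" that of the other arm. Power is 0.8. The one-sided two-proportion formula for 5% vs 2.5% gives 714 per arm. With the continuity correction, n' = (n/4)[1 + √(1 + 4/(n·d))]² with n = 714 and d = 0.025:

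178.5 × (1 + √1.224)² ≈ 792 per arm, or 1,584 in total, against the stated 1,582.

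Exact one-sided Fisher power at 791 per arm is 0.81. The sample size is not in dispute.

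**2. No prevention, selective loss only.** Take 5% of fetuses affected in both arms and 15% loss in both (Related risks). In the 4 mg arm, let a further fraction q of affected fetuses that would have been live born be lost. The value of q is an assumption; the documents give none. Per conception at 4 mg:

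- affected live births = 0.05 × 0.85 × (1 − q)
- unaffected live births = 0.95 × 0.85 = 0.8075
- live-birth recurrence = affected / (affected + unaffected)
- total loss = 1 − (affected + unaffected)

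Example, q = 0.5: affected = 0.02125; recurrence = 0.02125/0.82875 = 2.56%; loss = 17.1%.

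| q | Loss among affected fetuses, 4 mg | Live-birth recurrence, 4 mg (0.4 mg: 5%) | Total loss, 4 mg | Chance Fisher declares prevention (one-sided 0.05, 791 births per arm) |
|---|---|---|---|---|
| 0 | 15% | 5.0% | 15.0% | 4% |
| 0.1 | 23.5% | 4.5% | 15.4% | 9% |
| 0.2 | 32% | 4.0% | 15.8% | 20% |
| 0.3 | 40.5% | 3.6% | 16.3% | 36% |
| 0.5 | 57.5% | 2.6% | 17.1% | 79% |

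The third column should be set against the 2.5% design target. At the final one-sided boundary of 0.031 given under Interim analysis and study monitoring, the last column becomes about 6%, 14%, 28% and 71% for q = 0.1 to 0.5.

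**3. Would the miscarriage comparison show it?** Pregnancies per arm = 791/0.85 ≈ 931. For 15% vs 17.125%, the difference is 0.02125 with a standard error of about 0.0170. Two-sided at 0.05: z = (0.02125 − 1.96 × 0.0170)/0.0170 ≈ −0.71, so power is about 24%. For q = 0.1, 0.2 and 0.3 it is about 4%, 7% and 11%. At q = 0.5 the excess is about 20 losses (931 × 0.02125). The relative rise is 0.02125/0.15 ≈ 14%, while the smallest miscarriage change sized in Table 9 is 30%.

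**4. Would the weights correct it?** Two million women were simulated with no dose effect on cleft formation and q = 0.513, the value that gives exactly 2.5%. The risk ratio was 1.00 among conceptions and 0.50 among live births unweighted. It stayed at 0.50 with weights from baseline traits, and at 0.50 again when arm and its interactions were added. Fetal cleft status is not a maternal baseline trait, so weights of this kind cannot recover it.

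**The case against.** Several points on the other side stand.

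**The mechanism is possible, not shown.** The protocol speaks of spontaneous abortion in general and calls the suggestion unconfirmed. Nothing in it says that affected fetuses would be lost selectively. A rise in loss unrelated to cleft status leaves live-birth recurrence unchanged. The 50% row is extreme: loss among affected fetuses goes from 15% to 57.5% while unaffected fetuses are untouched. At 10% to 20% the false-positive chance is 9% to 20%.

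**For women's own choices, the reasoning is largely sound.** Subjects and staff are blinded and the pills look identical, so decisions to stay, conceive or continue should differ little by arm. The statement fails where the dose itself acts on fetal survival.

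**The protocol does look at fetal loss.** A reader might infer that a positive result could never be told apart from selective loss. That is too strong. Miscarriage is compared by arm, the monitoring board sees events by arm, and available material is examined and recorded. What is missing is any link from these to the primary result, and the miscarriage comparison has little power for this pattern.

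**The weights are not the fault.** A reader might infer that the plan builds its weights without treatment arm and that this is what lets the bias through. The documents support neither part. The covariate list is introduced as examples, so arm is unlisted rather than excluded. Step 4 shows that adding arm does not help against loss of affected fetuses. Arm matters only for selection through measured maternal traits, where the size is small. With the 30/70 risk mix, 7% and 4% recurrence, and women with clefts delivering at 60% in one arm and 80% in the other (all others 80%), the spurious difference is 4.90% − 4.73% = 0.17 points. With weights that ignore arm it is 0.18 points, and with arm-specific weights 0. The design difference is 2.5 points.

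**Conclusion.** The statement that randomisation removes bias from the births sample is wrong and should not remain as the justification for the primary comparison. The analysis conditions on live birth, a post-randomisation event that the protocol itself says the high dose may affect.

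With no prevention at all, selective loss of 10% to 50% of affected fetuses would make the primary test positive about 9% to 79% of the time, against about 4% with no selective loss. The miscarriage comparison would have at most about 24% power to signal it. These figures rest on 5% baseline recurrence, 15% baseline loss, 791 births per arm and the assumed range of q. They show how exposed the primary result is. They are no evidence that such loss occurs, and they do not question the planned number of births.

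**What to change.** 1. Delete the parenthetical claim about randomisation. State instead that the live-birth comparison can be biased if dose affects fetal survival.
2. Pre-specify a sensitivity analysis by arm with pregnancies as the denominator, counting NSCL/P found in miscarriages and stillbirths (forms FA09&10) as events alongside those in live births.
3. Report by arm the proportion of pregnancies that end in an unaffected live birth.
4. State that the primary result will be interpreted alongside items 2 and 3.
5. As a minor addition, name arm and its interactions in the propensity models, noting that this addresses only selection through measured maternal traits.

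The cost is extra analysis and reporting on data already collected, with no more subjects or visits. The drawback is that the pregnancy-level result is noisier and incomplete, because loss material is examined only when available. The number of losses examined in each arm should therefore be shown with it.

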#### Power analysis

Table
8 presents estimates of prospective number of births in the two study groups required for 70 and 80% statistical power and 30, 50, and 70% reductions in CL/P recurrence for alternative recurrence rates of 3, 5, and 7% in the 0.4 mg group. The 30% reduction represents a lower effect that is still very clinically significant, while the 70% represents an effect similar to that observed for NTD recurrence
[118]. The recurrence rates cover most of those reported in the literature and we use the 5% rate as a primary reference for our total suggested sample size given that it represents a proportional estimate of the 4 and 7% recurrence rates assuming that 30% of the study subjects will be women with clefts and 70% will be mothers to children with clefts. The power calculations are based on a Type I error probability of 5%. We use a one sided test as the recurrence rate in the 4 mg is not expected to exceed that of the 0.4 mg group given the converging evidence of protective effects of folic acid; a Fisher’s exact test is used.

**Table 8 T8:** Power analysis for primary hypothesis

**Baseline recurrence rate**	**% Reduction**	**Power**	**Total births**	**Total subject years**
*0.07*	70	0.8	524	5475
		0.7	418	4368
	50	0.8	1114	11641
		0.7	874	9133
	30	0.8	3324	34734
		0.7	2574	26897
*0.05*	70	0.8	742	7753
		0.7	590	6165
	50	0.8	1582	16531
		0.7	1240	12957
	30	0.8	4734	49467
		0.7	3666	38307
*0.03*	70	0.8	1254	13103
		0.7	996	10408
	50	0.8	2676	27962
		0.7	2096	21902
	30	0.8	8024	83845
		0.7	6210	64890

For a 50% reduction in a baseline rate of 5% recurrence, a total of 1582 births distributed equally across the two treatment groups are required. This number of births also provides acceptable power (0.75) to detect a 60% decrease in a 3% baseline recurrence rate, or a 40% decrease in a 7% baseline risk. If the 4 mg dose shows a preventive effect similar to that seen for NTDs (70%), the required numbers of births are halved regardless of the baseline recurrence risk (range from 524 to 1254 births for 80% power). The numbers of births required to observe a 30% reduction are about three times as large those for a 50% reduction.

This study may also allow evaluating secondary outcomes. The effect of the intervention on severity of clefting will be assessed. We will also stratify our analysis to examine differences in outcomes in the women born with CL/P independently from women who have a child with CL/P. The data from previous studies suggest a similar affect of folic acid supplementation in mothers with CL/P when compared to mothers who had a child with CL/P but as described below we will examine the groups together and separately.

Table
9 lists a few plausible effects and changes between the 4 and 0.4 mg groups and the total number of births needed to observe those effects with 80% power (type I error of 5%). Each of these (and others) will be studied as secondary outcomes. The DSMB will also monitor these outcomes to determine if significant untoward side effects are occurring (increases in miscarriage rates for example) but this is done independently of the research staff. All power simulations are based on a two-sided test except for the severity measure which is based on a one-sided test given that severity is expected to decrease with the higher dose.

**Table 9 T9:** Power to evaluate secondary outcomes

**Secondary outcome**	**Total births**
Birthweight (difference of 100 gm)*	928
Birthweight (difference of 200 gm)*	234
Gestational age (difference of 2 days*	2484
Gestational age (difference of 4 days*	622
Pre-eclampsia-Change by 40% from 10% baseline rate	1540
Pre-eclampsia-Change by 50% from 10% baseline rate	948
Severity (50% change from cleft lip with palate to cleft lip only in affected cases with 25% overall cleft prevention)	680
Miscarriage (30% change from 15% baseline rate)	1629
Miscarriage (50% change from 15% baseline rate)	562
* Assumes SD of 543 grams (birthweight) and 17.8 days (gestational age) as estimated in our studies in these populations.	

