#### Secondary hypotheses

The following secondary hypotheses will be evaluated:

An increase in serum and/or red cell folate levels in all women following daily supplementation with folic acid.

When compared to the 0.4 mg supplemented groups, the 4 mg per day group will have the following:

‐Greater increases in serum and/or red cell folate.

‐Decreases in the recurrence of NSCL/P in each of the following subgroups:

•Women with NSCL/P themselves

•Women with one or more children with NSCL/P

‐A decrease in the severity of NSCL/P in offspring of trial mothers.

‐No increase in twinning rates.

No increase in miscarriage rates.

No increase in rates of preeclampsia.

‐No increase in rates of other birth defects.

‐No decrease in birth weight

‐No decrease in gestational age

A decrease in recurrence of NSCL/P in the group of study subjects compared to an historical control group obtained from the populations served by the craniofacial clinics participating in the study.

A greater decrease in the recurrence of NSCL/P in the group of study subjects receiving 4 mg of folic acid when compared to the historical control group relative to that of the group receiving 0.4 mg when compared to the same control group.

Under separate funding we will examine the role of genes involved in folate metabolism on folate, B12 and homocysteine levels, as well as potential interaction between these genes and the supplementation dose. This project will also establish a resource to examine the long-term outcomes of infants exposed to high dose folic acid in utero.

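### Table 9 gives no direction for its pre-eclampsia and miscarriage sizes; the pre-eclampsia figures fit decreases, and all four are too small for the increases that the hypotheses and the DSMB concern

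*Protocol article*

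**What the plan says.** The Power analysis section introduces Table 9 as giving "the total number of births needed to observe those effects with 80% power (type I error of 5"%), and adds: "All power simulations are based on a two-sided test except for the severity measure". Four rows concern adverse pregnancy outcomes:

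- "Pre-eclampsia-Change by 40% from 10% baseline rate": 1,540 births
- "Pre-eclampsia-Change by 50% from 10% baseline rate": 948 births
- "Miscarriage (30% change from 15% baseline rate"): 1,629 births
- "Miscarriage (50% change from 15% baseline rate"): 562 births

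None of these rows says whether the change is up or down. Elsewhere the direction is explicit. The Secondary hypotheses section, comparing 4 mg with 0.4 mg, lists "No increase in rates of preeclampsia" and has a matching entry for miscarriage. The paragraph that introduces Table 9 says the DSMB will follow these outcomes "to determine if significant untoward side effects are occurring (increases in miscarriage rates for example"). The Related risks section raises a possible rise in spontaneous abortion with high doses and gives the same 15% expected rate that Table 9 uses as its baseline. The planned number of births, set by the primary hypothesis, is 1,582, split equally between the arms.

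**The concern.** A two-sided test treats both directions alike in its rejection rule, but not in its power. When the event rate is below one half, a relative rise has a larger binomial variance than a fall of the same size, so it needs more pregnancies to detect. A size worked out for a fall therefore overstates the power for a rise.

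For pre-eclampsia and miscarriage, the rise is the direction of interest. If the printed sizes are for falls, anyone using the table to judge how well the trial can detect harm from the higher dose gets too favourable a figure. This matters more because the hypotheses are of no increase: a non-significant comparison is the hoped-for result, and low power makes it easier to obtain.

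**Working it through.** **Inputs.** Two-sided alpha 0.05 and power 0.80 (Power analysis, text introducing Table 9); baselines 10% and 15% and the relative changes (Table 9); equal allocation and 1,582 births (Power analysis); Fisher's exact test for rates (Analysis plan), approximated for sample size by the continuity-corrected formula.

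**Formula, per arm.** With d = |p1 − p2| and p̄ = (p1 + p2)/2:

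n0 = [1.960·√(2p̄(1 − p̄)) + 0.842·√(p1(1 − p1) + p2(1 − p2))]² / d²

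n = (n0/4)·[1 + √(1 + 4/(n0·d))]²

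**Step 1: reproduce the printed pre-eclampsia figures.**

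- 10% to 6%: n0 = 720.9, n = 770.1, total 1,540 (printed 1,540; rounding each arm up gives 1,542).
- 10% to 5%: n0 = 434.4, n = 473.6, total 947 (948 with each arm rounded up; printed 948).

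Exact two-sided Fisher power for these decreases at the printed sizes is 0.804 and 0.809, so the figures are right for a fall.

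**Step 2: same method, same relative change, upwards.**

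- 10% to 14%: n0 = 1,034.9, n = 1,084.3, total about 2,170.
- 10% to 15%: n0 = 685.6, n = 725.0, total about 1,450.

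Exact Fisher power at 2,170 births for the first rise is 0.802. A one-sided 5% test would not rescue the 40% row: it needs about 1,630 births uncorrected and 1,730 corrected, still above 1,540.

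**Step 3: power for the rises at the printed pre-eclampsia sizes (exact two-sided Fisher).** At 1,540 births, 10% against 14%: 0.65. At 948 births, 10% against 15%: 0.61.

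**Step 4: miscarriage.** Totals in pregnancies, without and with continuity correction:

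| Change | Uncorrected | Corrected | Printed (births) |
|---|---|---|---|
| 15% to 10.5% | 1,724 | 1,812 | 1,629 |
| 15% to 7.5% | 556 | 608 | 562 |
| 15% to 19.5% | 2,212 | 2,300 | 1,629 |
| 15% to 22.5% | 848 | 902 | 562 |

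The printed 562 lies close to the uncorrected decrease (556). It also equals 607 × 0.925, the corrected decrease before rounding up, with the lower arm's 7.5% loss removed from both arms. The same rule gives 1,810 × 0.895 = 1,620 for the other row, not 1,629. Averaging the loss over the two arms gives 1,810 × 0.8725 = 1,579 and 607 × 0.8875 = 539, which match neither. No single convention yields both printed figures. Both nevertheless fall below every two-sided requirement for an increase counted in pregnancies. Converting those requirements to births with average loss does not close the gap: even the uncorrected values give 2,212 × 0.8275 = 1,830 and 848 × 0.8125 = 689.

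**Step 5: power for increases at the planned 1,582 (exact two-sided Fisher).**

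- Pre-eclampsia +40%: 0.66. Pre-eclampsia +50%: 0.84.
- Miscarriage +30%: 0.64 if 1,582 is taken as pregnancies. If 1,582 are births, the pregnancies behind them are about 1,582 / (1 − 0.1725) = 1,912, where 0.1725 is the average of 15% and 19.5%, and power is 0.72.
- Miscarriage +50%: about 0.97 with 1,582 pregnancies, and higher with more.

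**The case against.** The strongest reply is that the table claims less than a reader might infer. It says change, names no direction, and follows a sentence offering only that the study may allow secondary outcomes to be evaluated. A reader might infer from 1,540 lying just below 1,582 that the protocol claims 80% power for these safety signals at its planned size. It does not say so, and two rows (2,484 births for a 2-day difference in gestational age, 1,629 for miscarriage) already exceed 1,582. That stands: the defect is an unstated direction with figures that suit the wrong one, not a false claim about the whole trial.

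A reader might also infer that the miscarriage rows are demonstrably sizes for decreases. Step 4 does not support that; only their inadequacy for increases is shown. Nor are all four comparisons underpowered at the planned size, since the 50% rises keep more than 80%. The recruitment target is also larger than the minimum: 18,897 subject-years × 0.0957 is about 1,808 births, where power for the 40% rise in pre-eclampsia is about 0.72, still short of 0.80.

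Finally, safety oversight does not rest on Table 9. The DSMB reviews adverse events by arm at its meetings under its own charter, and nothing in the article says that a non-significant test will be read as proof of no increase. This limits the consequence, but does not make the printed sizes right for the direction in the hypotheses.

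**Conclusion.** The point holds for the four pre-eclampsia and miscarriage rows of Table 9. For pre-eclampsia the evidence is firm: both figures reproduce as decreases to within rounding, and the increases need about 41% more births (2,170 against 1,540) and 53% more (1,450 against 948). The direction is inferred from this match, because the document does not write it down. For miscarriage the conclusion is narrower: the derivation is unknown and the sizes are too small for increases.

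At the planned 1,582 births the practical shortfall is confined to the smaller effects: about 0.66 for a 40% rise in pre-eclampsia and 0.64–0.72 for a 30% rise in miscarriage, against 0.80. The results assume the protocol's baselines, equal arms and one analysed pregnancy per woman; the upper miscarriage figure also assumes that 1,582 counts births and that losses average over the arms. These rows do not set the sample size and touch neither the primary test nor the interim boundaries. The correction should be made, but the trial's main conclusion does not depend on it.

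**What to change.** State in Table 9 that the pre-eclampsia and miscarriage rows refer to increases, and replace the four sizes: about 2,170 and 1,450 births for pre-eclampsia rises of 40% and 50%, and about 2,210–2,300 and 850–900 pregnancies for miscarriage rises of 30% and 50%, with the formula named so that one value can be given. Count miscarriage in pregnancies, since a miscarried pregnancy is not a birth. Add the power for each increase at 1,582 births. Where the results are reported, give the confidence interval for the difference between arms beside any statement of no increase, rather than resting it on a non-significant test; at 1,582 births and a 10% rate its half-width is about 1.96 × √(2 × 0.10 × 0.90 / 791) = 0.030, or 3 percentage points.

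The cost is a recalculated table, some wording, and a less favourable stated power for safety. No change to recruitment or to the primary analysis is needed.
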